### Assessment and collection of outcomes

Participants will be assessed at baseline (day 0) and at the primary endpoint (day 28). During the trial, participants will return and be re-evaluated weekly on PTSD symptoms, BCBT, biopsychosocial questionnaires, and fluid biomarkers. In addition to exercise compliance, medications, and therapies, as well as any adverse events, compliance and feasibility will be evaluated at the weekly follow-up appointment. Cognitive assessment will only be repeated on the final evaluation. All data collection will occur at the Alfred Centre, Monash University. The full study schedule is included (Table 2).

**Table 2 Tab2:** Study schedule

Study assessments	Screening	Baseline	Intervention period	Weekly follow-up	Final visit
		Day 0	Day 1–6; day 8–13; day 15–20; day 22–27	Day 7, 14, 21	Day 28
Screening					
Eligibility questionnaire	X				
Enrolment					
Inclusion/exclusion criteria review	X	X			
Informed consent		X			
Allocate unique subject study identification		X			
Questionnaires					
Demographic data		X			
Medical history		X			
Ohio State University TBI Identification Method		X			
Godin Leisure-Time Exercise questionnaire		X		X	X
Medications		X		X	X
Current therapies		X		X	X
Exercise tolerance test					
Buffalo Concussion Bike Test (BCBT)		X		X	X
ECG recording		X		X	X
Biopsychosocial					
PTSD symptomology: PCL-5	X	X		X	X
Rivermead Post-Concussion Symptoms Questionnaire (RPQ)		X		X	X
Depression, Anxiety & Stress Symptom Scale (DASS-12)		X		X	X
The Alcohol, Smoking and Substance Involvement Screening Test (ASSIST-LITE)		X			X
Brief Pain Inventory (BPI)		X			X
12-Item Short Form Health Survey (SF-12)		X			X
World Health Organisation Quality of Life (WHOQOL-BREF)		X			X
Sleep-related inventory (SRI)		X			X
International Trauma Questionnaire (ITQ)		X			X
Neuropsychological assessment					
TOPF		X			
RAVLT		X			X
Digit Span		X			X
O-SDMT		X			X
TMT		X			X
Biomarkers					
Blood sample collection		X		X	X
Therapeutic intervention					
Dispense intervention		X		X	
Fitbit—dispense and instructions		X			
Record daily intervention sessions			X		
Return of Fitbit					X
Safety and feasibility assessments					
Adverse event monitoring		X		X	X
Feasibility					X

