**Methods:**

The target sample size of 120 women (aged 18–70) with a history of IPV (last instance > 3 months ago) and probable PTSD (via the PTSD Checklist for DSM-5; PCL-5) will be recruited via community advertisement in Melbourne, Australia. The trial will be completed at the Alfred Centre, Monash University. Participants will complete an exercise tolerance test via the Buffalo Concussion Bike Test and then will be randomised into either aerobic exercise or passive stretching. Participants will be instructed to complete 20 min of allocated aerobic exercise or stretching for 4 weeks and given a written diary and a Fitbit smartwatch to track program adherence. The primary outcome, PTSD symptoms via the PCL-5, will be collected at baseline, 1, 2, 3, and 4 weeks (primary endpoint). Secondary outcomes, including additional determinants of health (i.e. sleep, pain, substance use), cognitive testing, concussion-like symptoms in participants with a history of IPV-related brain injury, blood-based biomarkers, and feasibility and adherence to the prescribed program, will also be collected weekly at baseline, 1-, 2-, 3-, and 4-week follow-ups.

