### Data analysis

Primary and secondary outcomes will be assessed between groups at the primary endpoint (week 4) using two-sample *t*-tests (if normally distributed) or Mann-Whitney *U* tests (if not normally distributed). In addition, variables with multiple time points will also be assessed using generalised linear mixed-effects models. Models will be adjusted for confounders such as age, sex, baseline depression/anxiety/stress, history of migraine or other comorbidities, and cardiovascular fitness (Godin assessment). Feasibility (recruitment, retention, and completion rates), adherence (proportion), and safety (number and types of adverse events) will also be assessed. A statistician will be consulted in the events of missing data, any additional analysis, and to advise on interim analyses and stopping guidelines. Participants who do not complete the full 4-week intervention (i.e. lost to follow-ups) will be excluded from the primary endpoint analysis however will be retained in the descriptive analyses of the feasibility outcomes. Only the principal investigator will have the authority to terminate the trial.

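### The abstract and the assessment text make secondary questionnaires weekly (the abstract also cognition), but Table 2 schedules six questionnaires and the repeat cognitive tests only at baseline and day 28

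*Protocol article*

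**What the plan says.** Three places in the protocol article set the timing of the secondary outcomes.

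- **Abstract, Methods.** It lists "Secondary outcomes, including additional determinants of health (i.e. sleep, pain, substance use), cognitive testing, concussion-like symptoms" and, after adding biomarkers and feasibility, says that they "will also be collected weekly at baseline, 1-, 2-, 3-, and 4-week follow-ups".
- **Assessment and collection of outcomes, text.** Women return and are "re-evaluated weekly on PTSD symptoms, BCBT, biopsychosocial questionnaires, and fluid biomarkers". One exception is stated: "Cognitive assessment will only be repeated on the final evaluation".
- **Table 2 (Study schedule).** In the biopsychosocial block, the column for days 7, 14 and 21 is marked for PCL-5, RPQ and DASS-12. ASSIST-LITE, BPI, SF-12, WHOQOL-BREF, SRI and ITQ are marked at baseline and day 28 only. RAVLT, Digit Span, O-SDMT and TMT follow the same two-visit pattern, and TOPF is at baseline only.

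The Data analysis section compares groups at week 4 by a two-sample t-test or Mann-Whitney test, and adds that "variables with multiple time points will also be assessed using generalised linear mixed-effects models". It does not name those variables, so the visit schedule decides what goes into the models.

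**The concern.** The text and the table give different data-collection plans for the same instruments. The difference bears on the analysis because the rule for the mixed models depends only on how often a variable is measured. With four post-baseline values, a model can describe how sleep, pain or quality of life moves week by week in each arm. With one, it can estimate only the change from baseline to day 28. Sleep and quality of life are both named in the secondary objective, so these outcomes are not peripheral. A reader who later compares the report with the abstract would look for values at days 7, 14 and 21 that Table 2 never planned to collect.

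**Working it through.** No figure in the plan needs reproducing. The check is a count of visit marks in Table 2, set against the two statements in the text.

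Post-baseline values = marks at days 7, 14 and 21 (three if the weekly column is marked, otherwise none) + the mark at day 28 (one).

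| Outcome | Abstract | Assessment text | Table 2 |
|---|---|---|---|
| PCL-5 | weekly: 4 | weekly: 4 | 3 + 1 = 4 |
| DASS-12 | not named | weekly: 4 | 3 + 1 = 4 |
| RPQ | weekly: 4 | weekly, if counted as biopsychosocial | 3 + 1 = 4 |
| SRI (sleep), BPI (pain), ASSIST-LITE (substance use) | weekly: 4 | weekly: 4 | 0 + 1 = 1 |
| SF-12, WHOQOL-BREF, ITQ | not named | weekly: 4 | 0 + 1 = 1 |
| RAVLT, Digit Span, O-SDMT, TMT | weekly: 4 | final visit only: 1 | 0 + 1 = 1 |

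1. Six of the nine rows in the biopsychosocial block of Table 2 are not weekly. Counting baseline, each has 1 + 1 = 2 time points under the table and 1 + 4 = 5 under the text.
2. The protocol uses the term for a defined group: the subsection Biopsychosocial questionnaires lists seven instruments (DASS-12, SRI, BPI, SF-12, ITQ, ASSIST-lite, WHOQOL-BREF). Table 2 makes one of the seven weekly, DASS-12. The other six are exactly those in conflict.
3. All three health determinants that the abstract gives as examples (sleep, pain, substance use) are among those six.
4. For cognition, the assessment text and Table 2 agree, and the abstract stands alone.
5. The gaps in the table are not lost in extraction. The PCL-5, RPQ, DASS-12, bike test, ECG and blood rows keep their weekly mark, and the cognitive rows lack it just as the text says they should.

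Consequence for the models. If baseline plus day 28 counts as repeated measurement, the six instruments stay in the mixed models with one follow-up value instead of four. If it does not, they drop out. On either reading, no weekly course can be estimated for them under Table 2.

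Consequence for the week-4 test. The day-28 value exists under every reading, and so does the baseline value. The stated two-sample test ignores the baseline value. Adjusting for it reduces the outcome variance by a factor of about 1 − r², where r is the within-arm correlation between baseline and day 28. The documents give no r, so the gain is not sized here. It is positive whenever r is not close to zero.

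**The case against.** The strongest reply is that the assessment text is a summary. It does not claim that all the questionnaires are weekly, the biopsychosocial block of Table 2 does contain weekly instruments, and the paragraph closes by pointing to the table as the full schedule. This softens the conflict in that section. It does not remove it, because the protocol's own list under that name has seven members, only one of them weekly, and the paragraph makes an explicit exception for cognition and none for the six. It does not help the abstract, which names sleep, pain and substance use.

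A second reply is that the mixed-model rule follows whatever schedule is run, and that naming outcomes model by model is normally left to an analysis plan. That is fair: the rule is not wrong in itself. What is wrong is that the published text gives it two different inputs.

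A reader might infer two stronger points.

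- **Loss of follow-up data.** One could argue that a woman who leaves before day 28 gives nothing on the six instruments under Table 2. Data analysis already excludes women who do not complete the four weeks from the endpoint comparison, so interim questionnaires would not bring them back into it.
- **Volume of missing forms.** One could multiply the instruments by the visits and the women to get a large count. Such a count assumes full attendance and measures neither bias nor loss of precision.

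It could also be said that baseline adjustment does not follow from a schedule mismatch. As logic that is right. The proposal rests on its own ground: once the six outcomes are recognised as baseline/day-28 measures, their baseline value is the only other information on them, and the stated test leaves it unused.

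**Conclusion.** The conflict stands, for secondary outcomes only. Six questionnaires have four post-baseline values according to the text and one according to Table 2. The repeat cognitive tests have four according to the abstract and one according to both the assessment text and Table 2.

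A reader might infer that the main result is at risk. The documents do not support that: PCL-5 is weekly in all three places, and the week-4 comparison of every secondary outcome is possible on any reading. The effect is confined to what the supplementary mixed models can estimate and to whether the published plan will match the eventual report.

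The conclusion assumes that the visit marks in Table 2 came through intact, which the pattern of the other rows supports. It makes no assumption about which schedule the site follows, because the article does not settle that.

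**What to change.** Establish which schedule has been run since recruitment began in May 2024, and make the abstract, the assessment text and Table 2 agree with it.

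If it is Table 2:

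- State the weekly set explicitly: PCL-5, RPQ, DASS-12, bike test with ECG, and blood samples.
- State the baseline/day-28 set: ASSIST-LITE, BPI, SF-12, WHOQOL-BREF, SRI, ITQ and the repeat cognitive tests. Remove cognition and these questionnaires from the abstract's weekly claim.
- In Data analysis, limit weekly-trajectory models to the weekly set.
- Analyse the baseline/day-28 outcomes by a day-28 group comparison adjusted for the outcome's own baseline value, for example by analysis of covariance, instead of the unadjusted two-sample test.

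If the questionnaires have in fact been given weekly, correct their rows in Table 2 instead. They then belong with the weekly set.

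If Table 2 is what was run, the cost is a text correction and one or two sentences of analysis, with no new data. Recruitment was still open at submission and data collection is expected to run to May 2027, so the change can be made before the data are analysed.

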### Compliance to the intervention

Participants will be withdrawn from the study if there is a change in medications or if they are unable to attend follow-ups. Self-reported compliance to the intervention will be tracked at weekly follow-up visits via REDCap survey. Fitbit data can also verify adherence to exercise protocol and will be quantified via the following formula [61]:$$\mathrm{A}\mathrm{d}\mathrm{h}\mathrm{e}\mathrm{r}\mathrm{a}\mathrm{n}\mathrm{c}\mathrm{e}=\frac{{(\mathrm{v}\mathrm{o}\mathrm{l}\mathrm{u}\mathrm{m}\mathrm{e})}_{\mathrm{a}\mathrm{c}\mathrm{t}\mathrm{u}\mathrm{a}\mathrm{l}}}{{(\mathrm{v}\mathrm{o}\mathrm{l}\mathrm{u}\mathrm{m}\mathrm{e})}_{\mathrm{p}\mathrm{r}\mathrm{e}\mathrm{s}\mathrm{c}\mathrm{r}\mathrm{i}\mathrm{b}\mathrm{e}\mathrm{d}}}\times 100$$$$=\frac{{(\mathrm{H}\mathrm{R}\times \mathrm{t}\mathrm{i}\mathrm{m}\mathrm{e}\times \mathrm{f}\mathrm{r}\mathrm{e}\mathrm{q}\mathrm{u}\mathrm{e}\mathrm{n}\mathrm{c}\mathrm{y})}_{\mathrm{a}\mathrm{c}\mathrm{t}\mathrm{u}\mathrm{a}\mathrm{l}}}{{(\mathrm{T}\mathrm{a}\mathrm{r}\mathrm{g}\mathrm{e}\mathrm{t}\mathrm{H}\mathrm{R}\times 20\times 1)}_{\mathrm{p}\mathrm{r}\mathrm{e}\mathrm{s}\mathrm{c}\mathrm{r}\mathrm{i}\mathrm{b}\mathrm{e}\mathrm{d}}}\times 100$$

The numerator represents the volume of exercise performed divided by the volume of exercise prescribed to the participant. Volume actual is determined by multiplying weekly mean HR recorded during home exercise by weekly mean exercise time in minutes by the number of days per week out of 6 completed (i.e. 3 out of 6 days completed = 3/6 = 0.5). Volume prescribed was determined by multiplying weekly target HR by 20 min by days prescribed (every day excluding scheduled visit = 6/6 = 1). Participants who had an adherence rate of 66.67% or more were adherent, whereas participants with a rate lower than 66.67% were considered to be nonadherent [61].

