### Exclusion criteria

Subjects who are not willing or able to exercise due to health or personal reasons (e.g. orthopaedic injury, cervical spine injury, diabetes, known heart disease, or musculoskeletal injuries which could make exercise difficult or painful) via the Physical Activity Readiness Questionnaire (PAR-Q)Increased cardiac risk indicated by two or more of the following:Prior diagnosis of, or currently taking medication for cardiovascular (e.g. beta-blockers), metabolic, or pulmonary conditionsFamily history of myocardial infarction, coronary revascularisation, or sudden death before 55 yearsDiagnosis of hypertensionDiagnosis of hyperlipidaemiaSubjects with peripheral circulatory disordersHistory of prior head injury as defined by:Any head injury within the last 30 daysModerate or severe TBI, defined as a brain injury with an associated Glasgow Coma Scale score of 12 or lessDiagnosis of a neurological disorder (e.g. stroke, multiple sclerosis, epilepsy, brain tumour/cancer, encephalitis, dementia, movement disorder, spontaneous nystagmus, or brain surgery)History of drug or alcohol dependency or abuse within a year before screening by self-reportLimited English proficiency precluding completion of measuresSignificant psychiatric history (e.g. psychiatric hospitalisation, schizophrenia, history of legal trouble for violence)IPV history < 3 monthsNo PTSD symptomology at the initial visit (i.e. asymptomatic)Sustaining a head injury during the research periodNew (<1 month) or non-stable or pharmacological regimen prior to intervention (regimen must be maintained for the duration of intervention)Exercise-tolerant individuals with a current activity level equal to or greater than the proposed intervention as indicated by modified Godin Leisure-Time Exercise

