### Sample size

Although there are limited studies to base a statistical power calculation, the sample size was determined based on previous sample size estimates from trials using sub-symptom threshold aerobic exercise (STAE) interventions, which ranged from 46 to 96 participants [20, 21]. With an estimated drop-out rate of 20%, we will aim to recruit 120 participants [21].

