### Recruitment and screening process

Potential participants will be recruited through advertisement flyers in the community (e.g. hospitals, libraries, sports centres, women’s health and family violence services, community hubs, and rehabilitation clinics), social media, and by contacting participants from ongoing projects. When an individual provides consent to be contacted, a staff member on the research team will conduct a phone call to determine eligibility. During the phone call, participants will be assessed based on the inclusion and exclusion criteria. This will include PTSD symptoms, estimates of physical activity (i.e. Godin Leisure-Time Exercise) [22], cardiac risk, and individual safety in engaging in exercise (i.e. The Physical Activity Readiness Questionnaire; PAR-Q) [23].

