## Data collection, management, and analysis

### Trial allocation

This study is an open-label study; therefore, the investigator, site staff, and subjects will not be blinded to treatment allocation. A computer-generated randomisation schedule will be prepared by a statistician prior to the start of the study. Treatment allocation will be made per the randomisation list. After signing the informed consent form, subjects will be allocated a unique subject ID and administered the screening instruments via Research Electronic Data Capture (REDCap). A unique subject ID will be used to identify the subject throughout the study period and on all study-related documentation. After eligibility has been established, subjects will complete all baseline assessments followed by a simple randomisation in a 1:1 ratio to either the aerobic exercise or stretching group. Randomisation will be allocated sequentially based on the pre-determined randomisation schedule and according to their chronological order of inclusion in the study.

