### Attrition and adherence

To ensure attrition and program adherence, participants’ HR will be collected using a Fitbit Versa 3 and monitored using Fitabase (Small Steps Labs, LLC) [62], a software that synchronises and displays Fitbit data in real-time. If it is observed that a participant’s HR does not reach within the prescribed range, a member of the research team will check in via text or email. Participants will also be required to complete a written diary given at each follow-up to document the type of exercise they completed, how long they exercised for, and if any PPCS symptoms were triggered by engaging in exercise. Additionally, participants will be offered a $50 e-gift voucher at baseline and at each follow-up to encourage attendance. Participants will be withdrawn if they are unable to complete daily exercise or attend follow-ups.

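### Withdrawing women for a medication change or inability to keep exercising discards day-28 PCL-5 scores that could still be collected

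*Protocol article*

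**What the plan says.** Four statements in the protocol article bear on this point.

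- Compliance to the intervention sets the first rule: "Participants will be withdrawn from the study if there is a change in medications or if they are unable to attend follow-ups". No drug class, dose or reason limits the change.
- Exclusion criteria, on the pharmacological regimen: "regimen must be maintained for the duration of intervention". The condition therefore applies after randomisation as well as at entry.
- Attrition and adherence: "Participants will be withdrawn if they are unable to complete daily exercise or attend follow-ups".
- Data analysis: "Participants who do not complete the full 4-week intervention (i.e. lost to follow-ups) will be excluded from the primary endpoint analysis". These women remain only in the feasibility descriptives.

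The primary outcome is the PCL-5, a 20-item questionnaire, with day 28 as the primary endpoint. It is compared at week 4 by a two-sample t-test or Mann-Whitney test. In addition, "variables with multiple time points will also be assessed using generalised linear mixed-effects models".

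**The concern.** Randomisation follows the baseline assessments, so both triggers act on women who have already been allocated. Inability to attend may itself cost the assessment. A new prescription or an inability to go on exercising does not, and here the withdrawal rule is what ends follow-up.

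The week-4 test then compares only women who had none of these events. In a PTSD population a medication change may reflect worsening or improvement. Inability to continue is plausibly commoner in the aerobic arm, where the sub-symptom-threshold prescription has a symptom-based stopping rule for each session. If loss is related to outcome and differs by arm, the comparison is distorted. An analysis plan can redefine the analysis set, but it cannot create scores that were never taken.

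**Working it through.** **1. The rules read together.** A medication change leads to withdrawal from the study. Inability to complete daily exercise leads to withdrawal. Not completing the four weeks leads to exclusion from the primary endpoint analysis. No section provides for a PCL-5 after withdrawal. The bracketed reference to loss to follow-up in Data analysis does not rescue these women, because withdrawal is what ends their follow-up.

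**2. The plan's own figure.** Sample size cites earlier trials of 46 to 96 participants and states "With an estimated drop-out rate of 20%, we will aim to recruit 120 participants". The upper end reproduces the target: 96 / (1 − 0.20) = 120. The plan thus budgets for 120 × 0.80 = 96 analysed and 24 lost. It does not say how many of the 24 would be lost by rule.

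**3. Bias of the week-4 test (illustration).** Assumptions, none of them in the article:

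- 60 women per arm, no true effect, day-28 SD of 1;
- 20% overall loss, heavier in the aerobic arm;
- withdrawal driven by a normal variable correlated r = 0.3 to 0.5 with the day-28 score, higher scores being withdrawn.

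If a proportion p of an arm is withdrawn, the retained mean shifts by −r·φ(z)/(1−p), where z is the upper-p normal quantile. The error rate is P(|Z + bias/SE| > 1.96), with SE from the retained numbers and variances.

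- 25%/15%: 0.3178/0.75 − 0.2332/0.85 = 0.4237 − 0.2743 = 0.149. Multiplying by 0.3 and 0.5 gives 0.045 and 0.075 SD. With 45 and 51 retained, SE is 0.201 and 0.194, and the error rate 5.6% and 6.7%.
- 30%/10%: 0.3477/0.70 − 0.1755/0.90 = 0.4967 − 0.1950 = 0.302. This gives 0.091 and 0.151 SD. With 42 and 54 retained, SE is 0.202 and 0.195, and the error rate 7.3% and 12.1%.

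The bias falsely favours exercise. These are upper bounds, since all loss is taken as informative. When part of the loss is random, p is the rule-driven share divided by the fraction not lost at random (for example 0.125/0.90).

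| Rule-driven share of loss | Rule-driven split, aerobic/stretching | Bias (SD) | Two-sided error |
|---|---|---|---|
| All | 25%/15% | 0.04 to 0.07 | 5.6% to 6.7% |
| All | 30%/10% | 0.09 to 0.15 | 7.3% to 12.1% |
| Half (10% random per arm) | 12.5%/7.5% | 0.03 to 0.04 | 5.2% to 5.6% |
| Half (10% random per arm) | 15%/5% | 0.05 to 0.09 | 5.8% to 7.5% |
| Quarter (15% random per arm) | 6.25%/3.75% | 0.02 to 0.03 | 5.1% to 5.2% |
| Quarter (15% random per arm) | 7.5%/2.5% | 0.03 to 0.05 | 5.3% to 5.8% |

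Under this model, equal loss in both arms or r = 0 gives zero bias.

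**4. What the mixed model recovers.** It can use PCL-5 scores recorded before withdrawal. This was simulated with 400,000 women per arm, five visits, equal correlation of 0.6 or 0.8 between visits, withdrawal equally likely before each follow-up visit, and all loss informative.

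- Withdrawal depends only on the last recorded score: residual bias about 0 (at most 0.006 SD).
- Withdrawal depends on the unrecorded day-28 score: residual bias 0.01 to 0.05 SD (25%/15%) and 0.02 to 0.09 SD (30%/10%).

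**5. Precision.** Detectable difference by t-test at 80% power and two-sided 5% (both assumed, since the article states neither): 0.58 SD with 96 analysed. Keeping a quarter of the 24 gives 96 + 6 = 102 and 0.56 SD. Keeping half gives 96 + 12 = 108 and 0.54 SD.

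**The case against.** The strongest reply is that a stable regimen is a deliberate condition of the design. A drug change within four weeks would affect the PCL-5, and the article already screens out new or unstable regimens, so few events are likely. Whether to include values after a change is a choice of estimand. That stands as a reason to examine the stable-medication effect. It does not justify leaving the outcome uncollected: medications are recorded weekly, so a sensitivity analysis can answer that question, whereas removal after randomisation undermines the balance that randomisation gave.

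Second, the exercise trigger is less firm. Attrition and adherence does not repeat that withdrawal is from the study, and women below 66.67% adherence are classed as nonadherent without being withdrawn. This narrows that trigger to true inability, a group of unknown and perhaps small size. It does not touch the medication trigger.

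Third, the full protocol is not shown and might provide for data after withdrawal. It might. But the article states withdrawal and exclusion as rules, and nothing in it suggests an exception.

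Fourth, the size is uncertain. The arm split, the correlation and the rule-driven share are all assumed, and the medication rule applies to both arms. Worsening that prompts a medication change may also show in earlier weekly scores, which moves the mixed model towards its unbiased case. All of this is fair. The week-4 test has no such protection.

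**Conclusion.** The concern holds. For a medication change and for true inability to continue exercising, the article's rules discard a primary outcome that could still be obtained. For women unable to attend, much of the loss would occur anyway, so the rule explains only part of it.

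The consequence is conditional. Bias in the week-4 test runs from zero, with equal or outcome-unrelated loss, to 0.15 SD and a 12.1% error rate in the most adverse case examined; it is no more than 0.05 SD and 5.8% if a quarter of the loss is rule-driven. The gain in precision from keeping these women is modest. The change is worth making because the loss is avoidable, cannot be repaired afterwards, and continues while data collection runs (expected to end 16/05/2027). Confidence is medium, because the frequency of these events and their balance between arms are unknown.

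**What to change.** Amend Compliance to the intervention and Attrition and adherence so that a medication change or inability to continue may stop the allocated programme, as a clinical decision, but does not stop follow-up. Keep collecting the weekly and day-28 PCL-5 unless the woman withdraws consent, and let one who misses a weekly visit return at day 28. Offer a REDCap link where she cannot attend. It would help to say the same for a new head injury, which Exclusion criteria lists without stating whether outcome collection ends. In Data analysis, include these women as randomised in the primary comparison. If the effect without medication change is of interest, set aside values after a change in a sensitivity analysis.

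The cost is an ethics amendment, a survey link and a few remote contacts. Most of the means exist. Of the eligibility phone call, Recruitment and screening process says "This will include PTSD symptoms, estimates of physical activity". The screening instruments are already in REDCap, and daily smartphone and internet access is an inclusion criterion.

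There is a price. The estimate will include the effect of medication changes. A remote PCL-5 differs in setting from the on-site one, needs a matching edit to the statement in Assessment and collection of outcomes that all data are collected at the Alfred Centre, and should keep the distress support described under Informed consent. Women already withdrawn may not be recoverable, so the figures of 102 and 108 analysed are upper limits, and follow-up rules will differ before and after the amendment.

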## Interventions

### Aerobic exercise intervention

Participants determined to be exercise tolerant will be instructed to complete 4 weeks [24, 25] of aerobic exercise at the prescribed target heart rate (HR) of 50–65% of age-predicted HR [26, 27]. Participants determined to be exercise intolerant via the Buffalo Concussion Bike Test (BCBT) will be instructed to complete 4 weeks of STAE. The STAE prescription target HR will be 80% of the HR achieved at symptom exacerbation on the BCBT at the most recent visit. All participants will be required to complete 20 min of aerobic exercise of choice at home or in a gym at the individually prescribed HR, monitored by wearing a provided HR tracker (Fitbit Inspire 3). Participants performing STAE will be instructed to stop their exercise session if their symptoms increase by two or more points from their pre-exercise symptom level (on a 10-point Visual Analog Scale) or at 20 min, whichever comes first. All participants will be encouraged to perform 5 min of chosen warm-up and cool down. They will be told to rest apart from the prescribed exercise and not participate in other physically engaging activities. A 4-week intervention was chosen to align with the interventions’ previous interventions using aerobic exercise as a therapeutic intervention for brain injury [24, 25].$$Max\;Heart\;Rate\;=\;210\;-\;0.79\lbrack Current\;Age\rbrack$$$$\begin{array}{c}Goal\;heart\;rate\;=\;(Max\;Heart\;Rate\;-\;Resting\;Heart\;Rate)\;x\;Goal\;Percent\;Effort\;+\\Resting\;Heart\;Rate.\end{array}$$$$\begin{array}{c}\mathrm{Example}:\;45-\mathrm{year}-\mathrm{old}\;\mathrm{woman},\;\mathrm{resting}\;\mathrm{heart}\;\mathrm{rate}\;50\mathrm{bpm},\;\mathrm{goal}\;\mathrm{percent}\;\mathrm{effort}\;60\%\\210\;-\;0.79(45)\;=\;174\\(174-50)\;x\;0.60+50=124+/-10\mathrm{bpm}\end{array}$$

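### The adherence score uses absolute heart rate with no cap on heart rate or minutes, so aerobic-arm women well below their prescribed intensity can be classed as adherent

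*Protocol article*

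**What the plan says.** Under Compliance to the intervention, the protocol article gives the formula, explains each term and sets a cut-off.

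- Numerator: "Volume actual is determined by multiplying weekly mean HR recorded during home exercise by weekly mean exercise time in minutes by the number of days". The frequency term is a fraction of six days, so three sessions in a week count as one half.
- Denominator: "Volume prescribed was determined by multiplying weekly target HR by 20 min by days prescribed", with the days term equal to 6/6 = 1.
- Cut-off: "Participants who had an adherence rate of 66.67% or more were adherent".

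The target HR comes from Aerobic exercise intervention. Exercise-tolerant women are prescribed "aerobic exercise at the prescribed target heart rate (HR) of 50–65% of age-predicted HR". The equations and worked example that follow use heart-rate reserve: maximum minus resting HR, times percent effort, plus resting HR. For exercise-intolerant women on sub-symptom threshold aerobic exercise (STAE), "The STAE prescription target HR will be 80% of the HR achieved at symptom exacerbation on the BCBT at the most recent visit".

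Under Attrition and adherence, staff contact a participant whose "HR does not reach within the prescribed range". Nothing there changes her adherence score. Table 1 lists compliance as a secondary outcome to be verified by Fitbit, and Data analysis reports adherence as a proportion.

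**The concern.** Heart rate is not zero at rest. A ratio of absolute HR to target HR therefore starts well above zero before any exercise is done, and the cut-off is only two-thirds. The exercise-tolerant target is set on one scale (effort above rest) and scored on another (absolute beats per minute), so two-thirds of target HR is much less than two-thirds of the prescribed effort. Because the three factors are multiplied and two of them have no ceiling, long sessions can also make up for missed days.

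Exercise is unsupervised and done at the participant's discretion, so this score is the main objective summary of whether the aerobic intensity was delivered. If it passes women who stayed well below that intensity, a null PCL-5 result could be read as exercise having been done without benefit, when the dose was not reached.

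**Working it through.** **Inputs from the protocol article.** Worked example: age 45, resting HR 50, effort 60%, target 124 ± 10 bpm (band 114 to 134). Session 20 minutes; six days per week; cut-off 66.67%. STAE target: 80% of HR at symptom exacerbation. Bike test HR ceiling: 0.8 × (220 − age). Resting HRs other than 50 are assumptions, shown as a range.

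**Reproducing the plan's figures.** Max HR = 210 − 0.79 × 45 = 174.45, stated as 174. Goal HR = (174 − 50) × 0.60 + 50 = 124.4, stated as 124. The frequency example 3/6 = 0.5 also holds.

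**Score.** Adherence = HR × minutes × (days/6) ÷ (target × 20) × 100.

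**Below-range exercise in the worked example.** At 20 minutes on 6/6 days the cut-off is reached at 0.6667 × 124 = 82.7 bpm.

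- 83 bpm, 20 minutes, 6/6 days: 83/124 = 66.9%, adherent. This is 114 − 83 = 31 bpm below the band, and (83 − 50)/(174 − 50) = 26.6% of reserve against a goal of 60%.
- 113 bpm, 20 minutes, 5/6 days: 113/124 × 5/6 = 75.9%, adherent without entering the band.

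**Minutes offsetting days.** At target HR, 3/6 days × 26.7 minutes gives 0.5 × 26.7/20 = 66.75%, adherent; with 20-minute sessions the same woman scores 50%.

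**Resting HR.**

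- Worked example: 50/124 = 40.3%, not adherent. It passes only if sessions are logged as longer than about 33.1 minutes (34 minutes gives 68.5%).
- Exercise-tolerant, 50% effort, 20 minutes, 6/6 days: rest passes only if resting HR is at least half of max HR, about 87 bpm at age 45, 81 at 60 and 77 at 70.
- STAE: rest passes if rest/(0.8 × T) ≥ 2/3, that is, rest ≥ 0.533 × T, where T is HR at exacerbation. At assumed resting HRs of 60, 70 and 80, this covers T up to 112, 131 and 150 bpm. At age 45 the test ceiling is 0.8 × 175 = 140, so the largest STAE target is 0.8 × 140 = 112, and a resting HR of 75 scores 75/112 = 67.0%.

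**Reserve-based scoring, same example (target − rest = 74; 20 minutes, 6/6 days).**

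| Mean HR | Score now | (HR − rest)/(target − rest) |
|---|---|---|
| 50 | 40.3% | 0% |
| 83 | 66.9% | 33/74 = 44.6% |
| 113 | 91.1% | 63/74 = 85.1% |

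With time capped at 20 minutes, 3/6 days × 26.7 minutes falls back to 50%.

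**Cut-off rounding.** Four of six full sessions at target give 66.666…%, which is just below 66.67.

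**The case against.** The formula and cut-off are taken from a cited source, and changing them costs comparability. That is a reason to keep the published version as a secondary report, but it does not change how the arithmetic behaves with these targets.

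Several stronger readings are tempting, and the document does not support them.

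- A reader might infer that a woman who simply rests is called adherent. In the only worked example she scores 40.3%. Passing at rest needs a high resting HR, longer logged sessions or a low STAE threshold, and the protocol gives no distribution for any of these. She would also have to record rest as exercise, despite the diary, weekly survey and live Fitbit monitoring.
- A reader might infer that all three factors are unbounded. Days are expressed out of six and cannot exceed 1.
- A reader might infer that the check-in rule contradicts the score. It is an operational trigger for contact and classifies nobody, so a woman can trigger it and still pass a lenient volume threshold.
- A reader might infer that overshooting an STAE target rescues poor attendance. At the symptom threshold, 1.25 × 4/6 = 83.3%, but 4/6 days at target already sits at the cut-off, and 1.25 × 3/6 = 62.5% still fails.
- A reader might infer that the trial's adherence figure will be inflated by a known amount, or that the main result is affected. No achieved HR data are available. Data analysis excludes women who do not complete the four weeks, not those scored as nonadherent.

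What remains is the leniency on intensity, which needs no outside figure.

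**Conclusion.** The point holds in a limited form and should be corrected. With full attendance in the protocol's own example, the adherent class begins at 82.7 bpm, about 26% of reserve, against a prescribed 60%. This follows from the stated equations alone. The trade of minutes for days also follows directly from the formula. The resting-HR results for STAE and for older women depend on assumed resting HRs.

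The calculation follows the equations and example. If the target were read literally as a percentage of age-predicted maximum, the score would be more lenient: at age 45 and 50%, the target is 87 bpm and an assumed resting HR of 60 scores 68.8%.

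The effect is confined to a listed secondary outcome and to how the dose delivered is interpreted. How many women would be misclassified cannot be known from the document. The 4/6 rounding point is minor.

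**What to change.** For the aerobic arm:

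1. Replace HR/target with (HR − rest)/(target − rest), and cap the HR factor and the time factor (minutes/20) at 1 each. The frequency factor needs no change. In the worked example with full attendance, the cut-off then falls at 50 + 2/3 × 74 = 99.3 bpm, which is 40% of reserve, or two-thirds of the 60% goal.
2. Write the cut-off as 4/6.
3. Because 113 bpm still scores 85.1%, also report minutes within the prescribed range from the Fitabase HR data, wherever the protocol states a range.
4. Reconcile Aerobic exercise intervention with Attrition and adherence on what the prescribed range means for STAE. The former gives a single target and no band, so time in range cannot be computed for these women as written. This review proposes no band.
5. State how to score an STAE woman whose target is at or below her resting HR, since the new denominator is then zero or negative (at an assumed resting HR of 70, an exacerbation HR of 87.5 bpm or less).
6. Keep the published formula as a secondary report for comparison with its source.

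The cost is some reprogramming of Fitbit HR data already being collected, a resting HR for each woman (the goal HR equation already needs one for exercise-tolerant women), and probably a lower reported adherence proportion. The exercise prescription does not change.
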